## Abstract

**Background:**

At least 13% of mothers experience depression in the first postnatal year, with accompanying feelings of despair and a range of debilitating symptoms. Serious sequelae include disturbances in the mother-infant relationship and poor long-term cognitive and behavioural outcomes for the child. Surprisingly, treatment of maternal symptoms of postnatal depression does not improve the mother-infant relationship for a majority of women. Targeted interventions to improve the mother-infant relationship following postnatal depression are scarce and, of those that exist, the majority are not evaluated in randomised controlled trials. This study aims to evaluate a brief targeted mother-infant intervention, to follow cognitive behavioural therapy treatment of postnatal depression, which has the potential to improve developmental outcomes of children of depressed mothers.

**Methods/Design:**

The proposed study is a two-arm randomised controlled trial with follow-up to 6 months. One hundred participants will be recruited via referrals from health professionals including maternal and child health nurses and general practitioners, as well as self-referrals from women who have seen promotional materials for the study. Women who meet inclusion criteria (infant aged <12 months, women 18+ years of age) will complete the Structured Clinical Interview for the Diagnostic and Statistical Manual of Mental Disorders-IV-TR Axis I Disorders. Those with a clinical diagnosis of current major or minor depressive disorder and who do not meet exclusion criteria (that is, currently receiving treatment for depression, significant difficulty with English, medium to high suicide risk, current self-harm, current substance abuse, current post-traumatic stress disorder, current manic/hypomanic episode or psychotic symptoms) will be randomised to receive either a 4-session mother-infant intervention (HUGS: Happiness Understanding Giving and Sharing) or a 4-session attention placebo playgroup (Playtime) following a 12-session postnatal depression group treatment programme. Primary outcome measures are the Parenting Stress Index (self-report measure) and the Parent-child Early Relational Assessment (observational measure coded by a blinded observer). Measurements are taken at baseline, after the postnatal depression programme, post-HUGS/Playtime, and at 6 months post-HUGS/Playtime.

**Discussion:**

This research addresses the need for specific treatment for mother-infant interactional difficulties following postnatal depression. There is a need to investigate interventions in randomised trials to prevent detrimental effects on child development and make available evidence-based treatments.

**Trial registration:**

Australia and New Zealand Clinical Trials Register: ACTRN12612001110875. Date Registered: 17 October 2012.

**Electronic supplementary material:**

The online version of this article (doi:10.1186/1745-6215-15-385) contains supplementary material, which is available to authorized users.

## Background

Around 7.1% of new mothers have a major depressive episode during the first 3 months after delivery with an additional 12.1% of women suffering minor depression[1]. Postnatal depression (PND) is accompanied by a range of disturbing symptoms which can have a profound effect on the mother. Symptoms can include depressed mood, loss of interest, weight loss or gain, sleep disturbance, lack of energy, feeling agitated or slowed down, feelings of worthlessness or guilt, loss of concentration, and thoughts of death or suicide[2]. High anxiety is often co-morbid[3]. Symptoms of PND take on a particular significance due to the presence of an infant.

### Interactional difficulties accompanying postnatal depression

Current research strongly suggests that PND interferes with the behavioural and emotional exchanges between mother and infant[4]. Depressed mothers gaze less at their infants, rock their infants less, are less active and decisive, have less well-timed responsiveness, demonstrate lower levels of warm acceptance, are emotionally flat, and often disengaged[5–8]. Our earlier work demonstrated that infant development is powerfully shaped by the quality of the early mother-infant interaction following PND[9, 10]. These interactions are complicated, involving reciprocal, inter-dependent effects between child and mother. Brazelton and colleagues[11], Tronick and Weinberg[12], and Stern[13] describe the critical elements of a successful interaction, which includes an emotionally attuned and responsive mother. Emotional unavailability following depression may result in an escalating cycle of dysfunctional behaviours in both mother and child (for instance, maternal flat affect leading to gaze aversion in the infant leading to feelings of rejection in the mother and withdrawal).

### Importance of early mother-infant relationships

There is a growing awareness of the importance of early experiences in shaping infant brain development. Due to the plasticity of the brain at this early developmental stage, stressful experiences, including interactions with an un-attuned caregiver, may evoke permanent changes in brain organization[14–16]. The National Forum on Early Childhood Program Evaluation[17] concluded that infants of women with PND may experience “lasting effects on their brain architecture and persistent disruptions of their stress response systems” (page 3). Cognitive, emotional and social capabilities are all inextricably linked in brain development[18]. During the first 3 years of life, brain development is at its fastest and the brain is at its most malleable phase and most vulnerable to disrupted care-giving relationships. Intervening early is therefore imperative.

### Consequences of poor mother-infant interactions

Both short- and longer-term consequences have been reported for children of depressed and non-depressed mothers[19–22]. These can include poor social and cognitive outcomes from infancy to school age[6, 23–28], including poor psychological adaptation in adolescence[29], poor early school performance[30, 31], later anxiety[32], poorer self-regulatory capacities[33] and attachment insecurity[34] which in turn negatively affects subsequent interpersonal relationships[35], and has been linked with later behavioural problems[36]. As early as 3 months of age, infants of depressed mothers appear to generalise their depressed style of interaction to non-depressed adults[37].

Current evidence suggests that the mother-infant relationship is an important mediator between depression trajectories and child developmental outcomes (for example,[38]). In previous studies we demonstrated the critical importance of behavioural synchrony in the mother-infant interaction in the formation of attachment between mothers and their babies[39, 40]. More recently, we found that the quality (maternal responsiveness) of the early mother-infant relationship mediated poor child cognitive and behavioural outcomes at 4 years of age in a sample of women with PND[9]. Other evidence suggests ongoing difficulties to adolescence, particularly if depression is chronic[41, 42, 22].

### Treating mother-infant difficulties following postnatal depression

There is a critical need for brief interventions addressing mother-infant difficulties following PND, as treating maternal mood alone is not sufficient for improving mother-infant relationship difficulties[43]. A review of existing mother-infant interventions targeted at women with PND revealed that current studies of interventions were scarce, rarely used randomised controlled trial (RCT) methodology, are poorly evaluated, of long duration, and generally have not assessed infant outcomes[44–56]. In addition, many are not integrated with PND treatment of maternal mood symptoms. A brief mother-infant intervention that can change the developmental trajectory of infants of mothers with PND is of major public health significance and will potentially have important implications for preventing later emotional and behavioural disturbances in infants. In addition, this is most likely to improve outcomes if maternal depression is treated in order to facilitate the mother’s capacity to be emotionally available to her infant[7, 57]. This study aims to address the deficits in previous research: we use RCT methodology, an adequate sample size, an easily deliverable mother-infant intervention for mothers with PND that has been pilot tested, and assessment of both maternal and infant outcomes.

## Methods/Design

### Aims and objective

In a RCT, this study aims to evaluate the effectiveness of a targeted intervention (HUGS; Happiness, Understanding, Giving and Sharing) for enhancing mother-infant relationships.

The primary aim of the study is to determine whether women undergoing the combined PND treatment and HUGS programme will show greater improvement compared to a control group who received the PND treatment followed by an attention placebo playgroup (Playtime) in: 1) the observed quality of the mother-infant interaction; and 2) maternal reports of parenting stress, including feelings of attachment to their infant.

The secondary aim of the study is to determine whether infants undergoing the HUGS programme will show greater improvement compared to infants in the control condition in terms of: 1) difficult infant behaviour; and 2) early developmental milestones.

In addition, improvements in maternal mood are expected following the PND treatment and maternal mood is expected to continue to improve with the HUGS programme.

### Design

The proposed research is a multi-site, parallel, two-group RCT involving 100 participants (n = 50 in each condition) and will be conducted in line with CONSORT standards ([58, 59]; http://www.consort-statement.org/). Figure 1 shows the design of the study.

**Figure 1 Fig1:**
[figure not shown]
**Study flow diagram.** HUGS, Happiness Understanding Giving and Sharing; PND, postnatal depression.

### Procedure

Ethical approval has been obtained from Austin Health Human Research Ethics Committee (Project No. H2012/04745). Recruitment will be via referrals from health professionals including maternal and child health nurses and general practitioners, as well as self-referrals from women who have seen promotional materials for the study. They will be offered information sheets and consent forms where appropriate. After receiving informed consent, women will be screened with either the Edinburgh Postnatal Depression Scale[60] or the Whooley questions[61].

Women with a positive screening result (Edinburgh Postnatal Depression Scale ≥13 or an affirmative response to at least one of the two Whooley questions) will be assessed using the Structured Clinical Interview for the Diagnostic and Statistical Manual of Mental Disorders-IV-TR Axis I Disorders[62] to yield a diagnosis of current major or minor depressive disorder. Baseline questionnaires will be completed. Women who meet eligibility criteria will be randomly allocated to receive either HUGS or the attention placebo (Playtime) following the PND programme.

### Randomisation

Women are randomised prior to commencing the 9-week PND programme. A coded, double-blinded, variable-length permuted blocks randomised treatment allocation schedule produced by computer algorithm will be used. The allocation schedule will be stratified by site. It is not feasible to conceal the content of the intervention from those delivering the treatment. Participants will be blind to which condition is the intervention as both conditions will be presented as potentially beneficial.

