## Data analysis

### Power calculations

The primary outcomes are post-treatment/follow-up scores on mother-infant relationship measures: the PSI and PCERA. Based on published parameter estimates on the PSI (baseline = 282.46, σ = 41.25) from [name] and colleagues[10], a between-group difference of (δ) 33 points would take scores into the normative range on the PSI (that is, ≤250). To detect a change of 33 points, the sample size per condition is *n* = 15.7 (14.25/33)^2^ = 24.53. For the PCERA we wish to detect a medium to large effect size (2/3 SD). This is within the range of effect sizes reported for a longer mother-infant intervention measured with the PCERA[45, 46]. This yields *n* = 15.7 (1/.66)^2^ = 36.04, which rounds to 40. Taking the highest estimate (PCERA) and allowing 10% attrition, the adjusted group is *n** = *n*/(1-.10)^2^ = 49.38, which rounds to 50 depressed women in each condition.

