### Analyses

Data will be screened to: (i) check for data entry errors; and (ii) test the assumptions underlying parametric procedures. For each outcome, *a priori* treatment comparisons will be conducted by fitting models controlling for baseline values, to yield direct comparisons of the effectiveness of the two conditions. Intention-to-treat principles following CONSORT guidelines will prevent systematic bias[59]. Baseline data will be secured prior to allocation, and missing values will be scrutinized to check for non-random distribution and imputed at the case level using gold-standard maximum likelihood methods (Multiple Imputation). Primary analyses will be executed twice: once using observed data, and once using multiple imputation methods given by Schafer[74], so that all 100 participants will be analysed in their allocated treatment condition. To assess how non-compliance affects results, the dose-response relationship between session attendance and level of clinical improvement will be explored. Primary data analyses will be conducted fully blind to treatment allocation (via coded treatment labels).

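### Allocation is stratified by site, but the baseline score is the only covariate the analysis model names; adding site would recover a modest, conditional amount of precision

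*Protocol article*

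**What the plan says.** The Design section describes a "multi-site, parallel, two-group RCT involving 100 participants", with 50 women per condition. Under Randomisation, a "variable-length permuted blocks randomised treatment allocation schedule produced by computer algorithm will be used", and then: "The allocation schedule will be stratified by site".

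The Analyses section states the model once, for every outcome: "treatment comparisons will be conducted by fitting models controlling for baseline values". It goes on to cover intention to treat, multiple imputation, attendance and blinding of the analyst. Site does not appear in that section, either as a covariate or in connection with imputation. The text does not say that the baseline score is the sole covariate. The article gives no number of sites, no site sizes and no between-site variance.

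**The concern.** Permuted blocks within site keep the two arms close to balanced at each site, so differences between sites largely cancel out of the treatment contrast. A model without site does not know this. It counts between-site differences as residual noise and reports a standard error larger than the true sampling variability of the estimate.

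Three things are at stake: intervals wider than they need be, an actual error rate below the nominal one, and some lost power. There is also a point of consistency. The article states an adjustment set in advance, and that set does not match the randomisation it describes. An analyst who fitted the model as printed would leave out the stratum.

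**Working it through.** **The plan's own figure.** The constant 15.7 equals 2(1.96 + 0.8416)², which implies a two-sided 5% test and 80% power. For the PCERA, 15.7 × (1/0.66)² = 36.04, which the article rounds to 40. Then 40/(1 − 0.10)² = 49.38, rounded to 50 per arm. The figure reproduces. The formula is a plain two-sample one and takes no credit for stratification or baseline adjustment.

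**Inputs.** From the article: 40 analysed per arm and an effect of 0.66 SD. Assumed, because the article gives no value: s, the share of residual variance due to site after baseline adjustment, taken as 0%, 5%, 10% and 20%. Total residual variance is held at 1 and the effect is expressed in that SD.

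**Formulas.**
- Standard error reported without site: √(2/40) = 0.2236.
- True standard error under balance within site: √(2(1 − s)/40).
- Overstatement: 1/√(1 − s).
- Actual two-sided error rate without site: 2[1 − Φ(1.96/√(1 − s))].
- Power without site: 1 − Φ((1.96 × 0.2236 − 0.66)/true SE).
- Power with site: Φ(0.66/true SE − 1.96).

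Worked case, s = 10%: the true SE is √0.045 = 0.2121 and the overstatement is 1/√0.90 = 1.054. Power without site is 1 − Φ((0.4383 − 0.66)/0.2121) = 85.2%. Power with site is Φ(3.111 − 1.96) = 87.5%.

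| s (assumed) | SE overstated by | Actual error rate without site | Power without site | Power with site | Interval width, with / without |
|---|---|---|---|---|---|
| 0% | 0% | 0.050 | 83.9% | 83.9% | 1.000 |
| 5% | 2.6% | 0.044 | 84.6% | 85.7% | 0.975 |
| 10% | 5.4% | 0.039 | 85.2% | 87.5% | 0.949 |
| 20% | 11.8% | 0.028 | 86.6% | 91.0% | 0.894 |

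Power rises down both columns because total variance is held fixed while stratification removes more of it from the contrast. The cost of omitting site is the gap between the two power columns.

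**Check by simulation.** Permuted blocks of 2, 4 or 6 within equal sites, 80 women analysed, baseline-adjusted regression with and without site, 5,000 runs per setting (Monte Carlo standard error about 0.003 at an error rate of 0.05). Error rates without site at s = 5%, 10% and 20%:
- two sites: 0.050, 0.048, 0.041
- four sites: 0.046, 0.043, 0.029
- eight sites: 0.045, 0.043, 0.037

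With four sites, power without and with site was 83.8% and 84.4%, 84.9% and 86.8%, 86.4% and 90.3%. The direction agrees with the formulas. The effect is smaller with two sites, since a random draw of two site effects realises on average only half of the nominal share. At s = 0, including site made no visible difference to power.

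**On the PSI scale.** Take the article's SD ("baseline = 282.46, σ = 41.25") as the residual SD. This is itself an assumption, since baseline adjustment would reduce it. The 95% half-width without site is 1.96 × 41.25 × 0.2236 = 18.1 points. With site it would be 17.6, 17.2 or 16.2 points at s = 5%, 10% or 20%, against a target difference of 33 points.

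**The case against.** The strongest reply is that this rests on silence in a condensed article. Stratifying by site and adjusting for baseline are compatible, the sentence does not exclude a site term, and a full covariate list may sit in the full protocol or analysis plan. That stands as a limit: a reader might infer that site will be left out of the final analysis, and the article does not show this. It does not remove the point, because the article states its adjustment set in advance for every outcome, and the model as printed omits the stratum.

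Second, no input to the size comes from the article. The effect is nil if site does not predict outcome after baseline adjustment, and it is smaller with two sites. This stands, and it is why the size is given as a range starting at zero.

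Third, one might equate the omission with discarding 5% to 20% of the sample. That fits interval width only. The point estimate still benefits from the stratified allocation. The sample loss that matches the power loss is about 3%, 7% and 14% at s = 5%, 10% and 20%. Actually dropping from 40 to 32 per arm at s = 20%, with site in the model, would give about 84% power, against 86.6% when site is merely omitted.

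Fourth, one might conclude that the planned test is conservative overall. The article does not support this. Both conditions are delivered in groups and the stated model has no group term. Ignoring within-group correlation acts the other way: with assumed groups of 5 to 10 and an intraclass correlation of 0.02 to 0.05, the design effect 1 + (m − 1)ρ runs from 1.08 to 1.45 and the actual error rate from about 0.06 to 0.10. That is a separate issue and no reason to omit site, but the net direction is open.

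**Conclusion.** The point holds as a modest, conditional loss of precision. The allocation uses site and the model as printed does not. Other things equal, the standard error is then overstated by a factor of 1/√(1 − s): nothing at s = 0, 2.6% to 5.4% at an assumed 5% to 10%, and 11.8% at 20%. The corresponding power loss is about 0, 1, 2 and 4 percentage points with 40 analysed per arm.

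A reader might take this to mean that the trial is underpowered or its estimate biased. Neither follows. Power without site stays at 83.9% or more across the range in the formulas, and at about 83% with no site effect in the simulation, above the 80% implied by the sample size constant. Omitting site does not shift the estimate, and the required sample size does not change. The results rest on assumed values of s, roughly equal sites and near-balance within site.

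**What to change.** Extend the model sentence in the Analyses section so that the primary and secondary outcome models adjust for site, as the randomisation stratum, alongside the baseline score. Include site in the imputation model as well, so that the imputed-data analysis matches the observed-data one. If there are many sites, state in advance how very small ones will be pooled.

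The cost is a few words and one degree of freedom per additional site. With eight sites and 80 women analysed, for example, residual degrees of freedom fall from 77 to 70. If site turns out not to matter, practically nothing is lost. Naming site now also settles the choice before outcome data are seen. If the full protocol or analysis plan already includes site, the article's sentence only needs to be brought into line with it.

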### Inclusion and exclusion criteria

#### Inclusion criteria

Women with a clinical diagnosis of current major or minor depressive disorder as measured by the structured clinical interview, 18 years of age or older, and with an infant aged <12 months of age will be included in this study.

#### Exclusion criteria

Women fulfilling one or more of the following criteria will be excluded from participating in this study: currently receiving treatment for depression, significant difficulty with English, medium to high suicide risk, current self-harm, current substance abuse, current post-traumatic stress disorder, current manic/hypomanic episode or psychotic symptoms.

### Study outcome measures

The measures and time points of administration are shown in Table 1. The primary outcome measures are the Parenting Stress Index (PSI) and the Parent-child Early Relational Assessment (PCERA). All instruments to be used are established, well-validated, reliable and widely used, with well-described psychometric properties.

**Table 1 Tab1:** **Summary and timing of measures**

	Baseline	Post-PND programme	Post-HUGS/ Playtime	6-month follow-up
**Maternal measures**				
Socio-demographics: marital status, education, occupation, ethnicity, income, number of children, depression history, child health.	✓			
Edinburgh Postnatal Depression Scale[60]: 10-items to screen for probable depression.	✓			
Beck Depression and Anxiety Inventories[63]: 21 items measuring depression/anxiety symptoms.	✓	✓	✓	✓
Structured Clinical Interview for the DSM-IV-TR Axis I Disorders[62]: this diagnostic interview was developed to assess major Axis I disorders using nomenclature derived from the DSM-IV. Mood disorders, post-traumatic stress disorder, substance use disorders, and psychotic screening modules will be included.	✓			
Programme evaluation: questions asking about participants’ satisfaction with treatment.		✓	✓	
Services accessed: questions asking about services participants have accessed since joining the study.		✓	✓	✓

**Infant measures**				
Short Temperament Scale for Infants/Toddlers[67, 68]: 30 items assessing temperament. Includes subscales reflecting difficult infant behaviours (irritability, cooperation/manageability). Normative data available for Australian children.	✓	✓	✓	✓
Ages & Stages Questionnaire[69]: assesses early developmental milestones in five domains (communication, gross motor and fine motor skills, problem-solving, and personal-social skills).	✓	✓	✓	✓
Ages & Stages Questionnaire Social-Emotional[70]: assesses infants’ social and emotional behaviour.	✓	✓	✓	✓

DSM, Diagnostic and Statistical Manual of Mental Disorders; HUGS, Happiness Understanding Giving and Sharing; PND, postnatal depression.

